##### Protocol

The exercise schedule includes three parameters: frequency (three times a week), time (60 min per session) and content (10 min of evaluation and warm-up, 40 min of therapist-directed exercise therapy, and 10 min of relaxation). Natural breathing is recommended during exercise.

##### Exercise Intensity Monitoring

For a more clinical setting, the 40 min of exercise intensity is controlled by the therapist’s evaluation of the participant. According to RPE, moderate intensity aerobic exercise equals to 4–6 scores of the modified Borg Scale. Participants shall record their weekly home exercise and adverse events on given file (see Supplementary Additional File 4).

### Specific Notes

Participants accept intervention after baseline data collection. For 12 weeks, both groups receive supervised exercise, keep normal lifestyle and is not subjected to additional CLBP treatment. All participants are able to keep their routine medical visits with physicians. The research staff records any changes made to treatment but do not change or recommend changes in medical therapy. Participants will receive 50 yuan after the baseline assessment, 100 yuan for the final assessment, and, respectively, 50 yuan for two follow-up visits. Ensure the attendance of each participant for 3-month intervention through sign-in and telephone supervision. Participants with an attendance of 80% or above will be rewarded with an extra 100 yuan. Some participants may be absent on some weekdays, so we will plan to take a make-up session on weekends based on the number of participants to ensure the optimal attendance.

## Data Collection and Outcome Measurements

The outcomes and measurement timepoints are presented in Table 1. A demographic questionnaire which consists of participants’ characteristics (sex, age, body mass index, education background, and so on) and history of LBP will be completed before the intervention.

### Primary Outcome

#### Numerical Rating Scale–the Maximum and the Average Pain

We will use the NRS to measure the maximum and average pain intensity at 12 weeks. The NRS is an 11-point (from 0 to 10) scale, and a score of ‘0’ or ‘10’ means no pain or unbearable pain, respectively (Williamson and Hoggart, 2005; Maughan and Lewis, 2010). Participants will assess their scores according to pain experience. The NRS has an excellent test-retest reliability with an intraclass correlation coefficient (ICC) of 0.92 (Chiarotto et al., 2019).

#### Roland Morris Disability Questionnaire–Back-Related Function

Roland Morris Disability questionnaire is suitable for evaluating the short-term changes of back-related function after intervention. The questionnaire consists of 24 questions, involving eight facets of walking, standing, bending, lying, dressing, sleeping, self-care, and daily activities (Roland and Morris, 1983). ‘Yes’ (1 point) or ‘No’ (0 point) is answered to each question, and a high total score equates to poor back function. A reduction of 30% on RMDQ score from baseline is identified as minimal clinically important difference for CLBP (Jordan et al., 2006). The RMDQ has an excellent test-retest reliability with an ICC of 0.91 (Brouwer et al., 2004).

### Secondary Outcomes

#### Lumbar Quantitative Sensory Testing

Pain threshold is a predicator of chronic pain and can be used to assess muscle sensitivity (Fischer, 1987). Patients with CLBP had lower pressure pain thresholds than healthy people (Farasyn and Meeusen, 2005; Giesbrecht and Battié, 2005). We will use a hand-held digital manometer (FDX 25 Digital Force Gage, 100× 0.1N) to evaluate pressure pain thresholds of lumbar and lower extremity muscles in elderly people with CLBP. And also, we will use Pathway sensory assessment system (Medoc Ltd., Israel) to evaluate hot pain thresholds and cold pain thresholds.

#### 4-Stage Balance Test

The 4-stage balance test is recommended by Disease Control and Prevention to assess static balance in the elderly (CDC, 2017). Participants start in sequence with standing with feet side-by-side, then standing with half step (he instep of one foot touches the toe of the other foot), standing in tandem stance (the heel of one foot touches the toe of the other foot), and standing on one foot. Participants try to hold each position without any support for 10 s measured with stopwatch. If participants failed in one of the positions, the test will be terminated. A total time of less than 30 s indicates high risk of falling.

#### Cognitive Performance

Cognitive decline is an important concern with aging process. Each elderly participant is expected to finish cognitive tests. The Trial making tests (TMT) mainly focus on memory and executive function (Llinàs-Reglà et al., 2017). TMT-A is carried out by participants using a pen to connect random distributed numbers 1 to 25 in sequence, and TMT-B is carried out by connecting distributed letters A to L in sequence. Record the completion time of TMT-A and TMT-B, respectively. The Stroop color- word test is used to evaluate attention control, executive function, and working memory (Washburn, 2016; W. Wang et al., 2021). Participants will response to the color which is congruent, incongruent, or irrelevant with the random word meaning (Hyodo et al., 2012). Record the response time and accuracy.

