#### Inclusion and Exclusion Criteria

Target participants will be mainly community-dwelling elderly people who are living in Shanghai. The specific inclusion and exclusion criteria are listed in Table 2. The participants will quit the study if they have been diagnosed with severe diseases (such as heart failure) or serious adverse events occur during the experiment. Besides, the participants will be allowed to voluntarily quit as result of any of their own reasons. We plan to execute the following ways to access our participants as many as possible: (1) Distributing study recruitment flyers in nearby four communities with permission; (2) Sending study recruitment presentations to community healthcare center staff to help introduce potential participants; and (3) Disseminating the recruitment information through electronic communications and anyone interested can contact the recruiter by telephone.

**TABLE 2 T2:** Inclusion criteria and exclusion criteria.

Inclusion criteria	Exclusion criteria
Aged 50–80 years, can speak Chinese and complete the questionnaire survey.	Have practiced tai chi regularly for any reason within the past 6 months or who have practiced tai chi, yoga or qigong for nearly half a year to treat LBP.
Pain, at least 3 months, typically occurs in the area between the lower rib margins and the buttock creases, commonly accompanied by pain in one or both legs.	Have received guided physical therapy for LBP within half a year, including stretching, strength training, motor control training, and so on.
Have had back pain on at least half the time in the last 6 months.	Have specific causes or potential causes of LBP (e.g., sciatica, spinal stenosis, lumbar disk herniation, spondylolisthesis, recent vertebral fracture, and so on).
The average scores of numerical rating scale (in the range of 0–10) ≥3 and ≤8.	Have red flags of serious underlying systemic or visceral disease (e.g., inflammatory disorders malignancy, unexplained weight loss, infections, or recent trauma).
Back-related function scores of Roland-Morris disability questionnaire (in the range of 0–24) ≥5.	Pain in other parts of the body is greater than low back pain.
Have normal cognition or only mild cognitive impairment [the scores of Mini-Mental State Examination (in the range of 0–27) ≥24].	Had prior lumbar spine surgery.
Able to understand the learning process and complete the whole course.	Have history of drug and alcohol abuse.

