## Discussion

Finding an effective and inexpensive treatment for CLBP is valuable. Compared with the conventional non-invasive intervention for CLBP, TCQ is convenient and can be performed indoors and outdoors and by a single person or groups. For people of all ages, TCQ has the dual benefits of physical and mental conditioning. In this project, we will conduct an RCT to compare the effectiveness of TCQ with that of PT for CLBP. The TCQ practice program consists of eight movements for enhancing spinal stability and muscle strength of the waist and will be taught by professional teachers. Classification assessment and grouped-PT practice program based on patients’ functional performance and pain symptoms is carried out by licensed therapists. The intervention duration is 12 weeks, and 40 weeks of follow-ups is performed for the observation of long-term efficacy.

The strengths of this protocol are as follows. First, it will be the first RCT to compare modified TCQ with grouped-PT in patients with CLBP. The results of this trial will complement research in TCQ for LBP. Second, the 12-week intervention period and 40-week follow-up will be helpful in comparing the short- and long-term benefits of TCQ and PT. Third, by analyzing the medical expenses of the participants, the study will investigate whether TCQ has the benefit of saving medical costs. In addition, the study with large sample size will provide robust evidence of whether TCQ, rather than PT, can be a simple, effective, inexpensive and durable alternative therapy for chronic diseases. However, several potential limitations have been observed. First, all participants will not be blinded, and the recruitment criteria are limited to participants aged 50–80 years and without severe CLBP. Thus, the findings of study may not be appropriate for other age groups.

In conclusion, the purpose of this study is to estimate the effectiveness of TCQ in relieving pain intensity and improving back-related function and cognitive function on the basis of comparison with PT. The findings of this study will provide substantial evidence for TCQ as an effect alternative treatment for elderly people with CLBP.

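### TMT-B is described as a letters-only sequence, so its completion time cannot carry the executive-function reading that the protocol gives the test

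*Protocol article*

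**What the plan says.** All the relevant text on the TMT stands in one paragraph of the protocol article, Secondary Outcomes, Cognitive Performance.

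- Construct: "The Trial making tests (TMT) mainly focus on memory and executive function".
- Part A: "TMT-A is carried out by participants using a pen to connect random distributed numbers 1 to 25 in sequence".
- Part B: "TMT-B is carried out by connecting distributed letters A to L in sequence".
- Score: "Record the completion time of TMT-A and TMT-B, respectively".
- The other cognitive test in the paragraph, the Stroop colour-word test, "is used to evaluate attention control, executive function, and working memory". Its description names the congruent, incongruent and irrelevant conditions, and both response time and accuracy are recorded.

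Table 1 schedules the TMT and the Stroop test at baseline and at weeks 12, 26 and 52. Cognitive function is listed among the secondary outcomes in the Abstract and under Study Design. The closing paragraph of the Discussion includes it in the purpose of the trial: "improving back-related function and cognitive function on the basis of comparison with PT". Under Data Analysis, continuous secondary outcomes are compared between groups by an independent-samples t-test, with P below 0.05 taken as significant.

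**The concern.** The construct and the task do not match. The paragraph claims executive function for the TMT, but each part as described asks for one ordered run through one kind of symbol. Parts A and B differ only in the symbol and in the number of targets. A longer time on part B would reflect visual search, hand speed and familiarity with the order of the letters. None of that is specific to shifting between two rules.

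What is at stake is the interpretation of one secondary outcome. A between-group difference in TMT-B time would be reported as an effect on executive function, and the trial names cognitive function in its purpose. If the task was given as described, that label would be unsupported. An assessor who works from the published text, or a reader who tries to replicate the trial, would also run the wrong task.

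**Working it through.** The protocol gives no numerical figure for the TMT, so the check is a count and a comparison of passages. The sample size is reproduced first, only to show that it does not depend on this point.

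**1. Sample size (Sample Size section).** Inputs: standardised effect 0.54, two-sided alpha 0.05, power 0.80, attrition 20%. The independent-samples t-test with the noncentral t distribution gives 54.81, so 55 per group and 110 in total. Inflating for attrition, 110 / (1 − 0.20) = 137.5, which rounds up to 138, or 69 per group. The stated figure is reproduced. It rests on the RMDQ effect size, and no cognitive test enters it.

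**2. Targets per part, as described (Cognitive Performance).**

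| | Symbols | Targets | Sequences to hold | Switching stated |
|---|---|---|---|---|
| Part A | numbers 1 to 25 | 25 | one | no |
| Part B | letters A to L | 12 | one | no |

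Part B therefore has 12/25 = 48% of the targets of part A and the same task structure. The text contains no demand that is present in B and absent from A, other than the change of symbol.

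**3. Comparison within the same paragraph.** The Stroop description names the condition that makes it an executive test, namely a colour that conflicts with the word. The TMT-B description names no corresponding element.

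**4. Is a dropped phrase plausible?** If part B alternates (1-A-2-B and so on) and ends on a number, the letters A to L (12) need 13 numbers, and 12 + 13 = 25. That equals the target count of part A. The printed letter range therefore fits an alternating sheet whose number half was left out of the description. The alternating form is taken here from general knowledge of the standard test. The protocol does not reproduce the sheet, and the source it cites is not available.

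**5. Exposure.** With 138 participants and four scheduled visits, up to 138 × 4 = 552 administrations depend on this definition, before attrition.

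**The case against.** The strongest reply is that a journal article gives each instrument a sentence or two, so a short description does not show that participants receive a different test. The count in step 4 supports that reply, and it stands as the likeliest explanation. It does not remove the point. The text does not merely omit detail. It states what part B is, with its symbols and range, and the stated task does not match the stated construct.

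It can also be said that executive function is covered by the Stroop test at all four visits. That is correct and limits the damage: a conclusion on executive function could still rest on the Stroop test. It does not make the TMT-B label valid.

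Three stronger readings are tempting, and the documents do not support them.

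- A reader might infer that a B-minus-A contrast is spoiled. None is planned; the two times are recorded separately.
- A reader might infer that Latin letters disadvantage these participants. Table 2 requires that they speak Chinese and can complete the questionnaires, and nothing shows that they do not know the letters.
- A reader might join this to the cognitive entry rule in Table 2, "the scores of Mini-Mental State Examination (in the range of 0–27) ≥24", and infer that only scores of 24 to 27 are eligible. The rule is a lower bound with no ceiling, the same row expressly admits normal cognition, and the bracket only describes the scale. The documents do not give another maximum. The printed range is worth checking against the form in use, but it is not a finding.

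**Conclusion.** The point holds for the TMT only. As written, TMT-B is a 12-target single-sequence task beside a 25-target single-sequence task. Its completion time is then a second speed measure and cannot support an executive-function conclusion from the TMT, which leaves the Stroop test as the only executive measure.

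The mismatch between task and construct is visible in the text itself. What cannot be settled from the document is whether the wording or the test sheet is at fault. If only the wording is wrong, the data are sound and the correction is editorial. If the sheet is letters-only, the TMT-B results need a different label. The co-primary pain and RMDQ outcomes, the allocation, the sample size of 138 and the primary analysis are unaffected in either case. A clarification is warranted, limited to one of many secondary measures.

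**What to change.** Under Cognitive Performance, define TMT-B as connecting numbers and letters in alternation (1-A-2-B and so on), and confirm that the sheet used by the assessors matches that definition. If a letters-only sheet is really in use, keep the description, state that TMT-B is a speed measure, do not report it as executive function, and rest any executive-function statement on the Stroop test.

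The cost is one sentence of text and possibly a replacement test sheet. No extra visit, participant or analysis is needed. If data have already been collected on a letters-only sheet, the sheet should not be changed without recording which version each participant received at each visit, because the two versions' times would not be comparable.

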#### 6-Min Walk Test

The 6-min walk test (6MWT) is in measuring the distance that a participant can quickly walk on a flat and hard surface in 6 min. The distance recorded in meters will reflect the functional exercise level of daily physical activities (Peppin et al., 2014).

#### Geriatric Depression Scale

The 15-item Chinese revision of the Geriatric Depression Scale (GDS) is suitable for assessing the level of elderly depression. According to the items on the scale, participants answer ‘yes’ or ‘no’ to describe their feelings in the last 2 weeks. The higher the score (closer to 15) is, the higher level of depression is (Park and Kwak, 2021). The GDS has an excellent internal consistency (Albiński et al., 2011).

#### Self-Rating Anxiety Scale

The Self-rating Anxiety Scale (SAS) is a self-reported scale, in which items tap affective and somatic symptoms. Each item of the scale is rated by participants according to their actual status within the past week, using a 4-point scale ranging from 1 (none or a little of the time) to 4 (most or all of the time) (Shimada et al., 2016). Higher score indicates greater severity of anxiety. The SAS has a satisfactory internal consistency with a Cronbach’s alpha of 0.83 (Dunstan and Scott, 2020).

#### Pain Catastrophizing Scale

The Pain Catastrophizing Scale (PCS) is designed to assess catastrophic thinking associated with pain among patients with chronic pain (Wheeler et al., 2019). Participants will self-report 13 items related to painful experiences and the answer will be rated on a 5-point Likert scale from 0 (not at all) to 4 (all the time). A total score above 30 indicates clinically relevant level of catastrophizing. The test-retest reliability is excellent with an ICC of 0.94 (Xu et al., 2015).

#### Tampa Scale for Kinesiophobia

The Tampa Scale for Kinesiophobia (TSK) is a 17-item self-report measure to assess pain-related fear and is used extensively in patients with persistent LBP (Roelofs et al., 2004). The scale is rated on a 4-ponit Likert scale from 1 (strongly disagree) to 4 (strongly agree). A high score indicates high level of the fear of activity or reinjury. The TSK has a good reliability with an ICC of 0.86 (Wei et al., 2015).

#### Pittsburgh Sleep Quality Index

The Pittsburgh Sleep Quality Index (PSQI) can be used in assessing sleep quality and disturbances. The index ranges from 0 to 21 and consists of 24 questions covering seven domains. The lower the index is, the better the sleep quality or the lower the disturbance in sleep is (Mollayeva et al., 2016). The PSQI has an excellent test-retest reliability with a correlation coefficient of 0.77 (Tsai et al., 2005).

#### Short-Form 12

The Short-Form 12 (SF-12) is a brief health-related quality of life questionnaire. The questionnaire measuring eight domains can be used in calculating physical and psychological scores (Ware and Sherbourne, 1992). It is widely used in community-based health surveys and outcome assessment of physical and mental illnesses. Low scores indicate poor health status. The SF-12 shows satisfactory internal consistency both in the physical component summary (Cronbach’s alpha = 0.81) and mental component summary (Cronbach’s alpha = 0.83) (Su and Wang, 2019).

#### General Perceived Self-Efficacy Scale

The scale has 10 items, each of which is scored in integers from 1 (completely incorrect) to 4 (completely correct) (Zotti et al., 2007). High scores indicate better confidence to handle various things. General Perceived Self-efficacy Scale (GSES) can be considered a predictive variable of outcomes and an outcome itself. We use it to reflect participants’ confidence in their capability to increase self-management of chronic pain and perform daily coping tasks. The GSES has an adequate test-retest reliability with a correlation coefficient of 0.75 (Wu et al., 2004).

#### Expenses for Healthcare Monthly

To analyze the cost-effectiveness of TCQ and PT, we will collect participants’ expenses for treating LBP or other diseases monthly since the start of the intervention. We expect that practicing TCQ will reduce the cost for treating chronic diseases and improve quality of life.

#### Global Perceived Effect

Global Perceived Effect (GPE) numerical rating scale consists of seven choices (from 1 to 7 points), each representing the overall improvement in the participants’ symptoms after they completed the trial (Kamper et al., 2010). A good improvement indicates a high score. It can be useful in understanding the strengths and shortcomings of outcome measures for research. The participants will be asked to rate the degree of improvement or aggravation in their conditions since the beginning of the intervention. The GPE has an excellent test-retest reliability with an ICC of 0.90 (Kamper et al., 2010).

We will record the number of classes the participants attend and the reasons for absence. In addition, adverse events, which are related to interventions and home exercise, will be recorded (see Supplementary Additional Files 1, 4 for details).

## Data Management and Analysis

### Data Management

After recruitment, the researchers will replace the participants’ names with numerical codes in order to protect their privacy. Their data will be collected at baseline and week 12, 26, and 52, respectively. Two professional data workers are responsible for entering their paper files into the same database and cross-checking them for data’s accuracy. Eventually, all paper files and encrypted electronic files will be kept and backed up by the researcher leader. These files will be maintained in storage for 3 years after completion of the study.

### Data Analysis

Intention-to-treat analysis will be performed regardless of adherence. Microsoft excel 2016 and IBM SPSS Statistics 20.0 (SPSS Inc., Chicago, IL, United States) will be used in data analysis. Continuous variables (e.g., age, body mass index, NRS score, and RMDQ score) will be represented as mean ± standard deviation and be compared using analysis of the independent samples *t*-test. We will use the chi-squared test to analyze the categorical variables (e.g., gender, marital status, smoking, and exercise habits) between the TCQ group and PT group. The baseline demographics characteristics differences between groups will be compared using analysis of *t*-test, variance (ANOVA) or chi-squared tests. If potential confounding factors including gender, age, body mass index, smoking, exercise habits, etc., are present, we will prespecified an adjusted analysis, by using multiple linear regression. At the same time, missing values at week 12, 26, and 52 will be imputed using the multiple imputation.

The co-primary outcomes are the measurement of minimal clinically important difference in NRS and RMDQ scores in two groups after the 12-week intervention, and the paired-sample *t*-test will be carried out for the comparison of the differences. For secondary outcomes, the difference of continuous variables between groups will be compared using the analysis of independent-samples *t*-test. Expenses for LBP or other disease will be explored for cost-benefit analysis. Participants’ global perceived effect, adherence, and health-related quality of life will be compare using appropriate regression. The Fisher exact test will be used to compare adverse events. For the follow-ups phase, two-way repeated-measures analysis of variance (group × time) will be carried out to assess the differences of the primary outcomes (NRS score and RMDQ score) between the two groups. In all analyses, a *P*-value of <0.05 will be considered statistically significant.

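### Covariate adjustment is conditional with an open list, and the between-arm t-tests omit the baseline score; one fixed baseline-adjusted model that respects the communities would be better

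*Protocol article*

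**What the plan says.** All of the following is in the Data Analysis section of the protocol article, unless another section is named.

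- **Baseline tests.** The arms are tested against each other by t-test, ANOVA or chi-squared test: "The baseline demographics characteristics differences between groups will be compared using analysis of" (the sentence then lists them).
- **Adjustment rule, in the next sentence.** "If potential confounding factors including gender, age, body mass index, smoking, exercise habits, etc., are present, we will prespecified an adjusted analysis". The adjusted model is to be a multiple linear regression. No criterion is given, and nothing says whether the adjusted or the unadjusted result leads.
- **General rule for continuous variables.** "Continuous variables (e.g., age, body mass index, NRS score, and RMDQ score) will be represented as mean ± standard deviation", with comparison by independent-samples t-test. NRS and RMDQ are named here.
- **Secondary outcomes.** The test is again the unpaired t-test: "For secondary outcomes, the difference of continuous variables between groups will be compared using the analysis of independent-samples" (the sentence ends with its name). Global perceived effect, adherence and quality of life are instead sent to an unspecified regression.
- **Co-primary outcomes.** "The co-primary outcomes are the measurement of minimal clinically important difference in NRS and RMDQ scores in two groups after the 12-week intervention", tested by a paired-sample t-test.
- **Follow-up.** "two-way repeated-measures analysis of variance (group × time) will be carried out to assess the differences of the primary outcomes". The time points in the model are not stated.

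Table 1 shows NRS, RMDQ and most secondary scores collected at baseline. The Randomization and Blinding section allocates four communities, two to each arm, and then recruits participants within the allocated community.

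**The concern.** An analysis whose use and content depend on what the baseline data show is chosen after the data are seen, even though the text calls it prespecified. If the baseline tests are the trigger, the model is selected by significance. If they are not, the rule has no stated trigger and the analyst's discretion is wider. In both cases two sets of results can exist without a rule on which one counts.

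The baseline value of the same score, usually among the strongest predictors of a follow-up score, is missing from the named covariates. With four allocated communities and recruitment after allocation, the arms may well differ in starting pain and disability. An unadjusted comparison of follow-up scores carries part of that difference into the treatment estimate.

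**Working it through.** **Inputs from the protocol.** Two-sided alpha 0.05, power 0.80, effect size 0.54, 20% attrition, 138 participants or 69 per arm (Sample Size); four communities, two per arm (Randomization and Blinding). **Assumed, because the document gives no value:** baseline to week-12 correlation ρ of 0.3, 0.5 and 0.7, equal SDs at both times, and an intracluster correlation (ICC) of 0.01 to 0.05.

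**1. The plan's own figure.** A two-sample t-test (noncentral t) with 55 per arm and effect size 0.54 has power 0.801. Then 55 / 0.8 = 68.75, rounded up to 69 per arm, 138 in total. The stated number reproduces exactly, so there is no arithmetic error in the sample size. It uses no baseline correlation.

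**2. Precision at the individual level.** With unit SD, the variance per participant is 1 for a week-12 score, 2(1−ρ) for a change score and 1−ρ² for ANCOVA. ANCOVA against change is therefore (1−ρ²)/(2(1−ρ)) = (1+ρ)/2.

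| ρ | ANCOVA vs week-12 score | Reduction | ANCOVA vs change score | Reduction |
|---|---|---|---|---|
| 0.3 | 0.91 | 9% | 0.65 | 35% |
| 0.5 | 0.75 | 25% | 0.75 | 25% |
| 0.7 | 0.51 | 49% | 0.85 | 15% |

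With 55 completers per arm and 110 − 3 = 107 error degrees of freedom, ANCOVA power is 0.837 / 0.900 / 0.976 if 0.54 is in week-12 SD units, and 0.936 / 0.900 / 0.861 if it is in change-score SD units. Without the covariate it is 0.801 in each case.

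**3. Behaviour of a significance trigger.** If each of the five named factors is tested at 0.05, independently and under individual randomisation, the chance of at least one significant result is 1 − 0.95⁵ = 0.226.

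A trigger also misses imbalance that matters. With 69 per arm the critical t on 136 df is 1.978, so an observed baseline difference must exceed 1.978 / √(69/2) = 0.34 SD to be significant. An imbalance of 0.30 SD gives t = 0.30 × √34.5 = 1.76 and passes unnoticed. An unadjusted week-12 comparison then carries 0.30ρ = 0.09 / 0.15 / 0.21 SD into the estimate, which is 17% / 28% / 39% of 0.54.

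**4. Simulated rule.** The rule was to adjust for the baseline score only if its own baseline test has p < 0.05 (8,000 trials per setting, 55 per arm, individual randomisation, ρ = 0.3 / 0.5 / 0.7). Type I error was 0.048 / 0.045 / 0.035. Power was 0.80 / 0.81 / 0.83, against 0.84 / 0.90 / 0.98 for ANCOVA in every trial.

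**5. Effect of the communities.** Completers per community are 55 / 2 = 27.5, so the design effect is 1 + 26.5 × ICC: 1.27, 1.53 and 2.33 at ICC 0.01, 0.02 and 0.05. The effective number per arm falls from 55 to about 43, 36 and 24. With the 4 − 2 = 2 degrees of freedom that four communities allow, and 1−ρ² applied to the whole variance, power at ρ = 0.5 goes from 0.30 to 0.37 at ICC 0.01 and from 0.20 to 0.24 at ICC 0.05.

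**6. Community as a fixed effect.** Intercept, arm and three community indicators make 5 columns of rank 4, because community is nested in arm. The arm effect is then not estimable.

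**The case against.** Several parts of the opposing case stand.

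- A reader might infer that the outcome tests as a whole ignore the baseline score. The text does not support that. The co-primary paired t-test uses baseline by differencing, Sample Size speaks of change from baseline, and the group by time ANOVA may include baseline. Quality of life goes to a regression with unstated terms. The omission is established for the independent-samples t-tests. The fault of the paired test is a different one: it compares within an arm, not between arms.
- The link between the baseline tests and the adjustment is inferred from two adjacent sentences. The 23% in step 3 depends on that reading and on individual randomisation, which this trial does not use.
- A reader might infer an inflated type I error. The simulation shows none; the rule was slightly conservative. It covered one covariate only.
- The article is condensed, and a final covariate list may sit in an analysis plan that is not shown. That would excuse silence. It does not excuse a stated rule that makes adjustment conditional and leaves the list open.

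**Conclusion.** The point holds in limited form. The adjustment rule as written is not prespecified, and the between-arm t-tests leave out a baseline score that the trial collects. The cost is analyst discretion, lost precision and weak protection against imbalance.

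The size rests on an assumed correlation of 0.3 to 0.7: 9% to 49% lower variance against a week-12 comparison, and 35% to 15% lower against a change-score comparison. These are individual-level upper bounds. It would be tempting to conclude that adjustment lifts power from 80% to 90%. That figure needs ρ = 0.5 and individual randomisation, and the second contradicts the allocation of four communities. The sample size of 138 is not shown to be miscalculated by this point.

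**What to change.** Remove baseline differences as a trigger for adjustment; baseline characteristics can still be described. For each continuous outcome measured at baseline, fix one between-arm model in advance: follow-up score on arm, baseline value of the same score and a closed covariate list. State that this is the leading result, and run it on the multiply imputed data.

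Handle community as a random effect, with degrees of freedom suited to four clusters, or by a cluster-level analysis. Do not enter it as a fixed effect beside arm.

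The cost is wording and one error degree of freedom for the baseline score, plus those for whatever closed list is chosen. The scores are already collected. The change does not solve having only two communities per arm, and the paired t-test needs its own correction.
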